### **3.8 Justification of choice of the study population**

This study will be conducted on individuals living with T1D. Only people with T1D using a Swiss-approved AID system will be included. No vulnerable populations, such as neonates, pregnant women, children, prisoners, institutionalized individuals, or others who may be considered vulnerable populations, will be included in this study. More details about the eligibility criteria and recruitment of the participants are described in the following sections (**See Chapters 7 and 11**).

## 4. STUDY OBJECTIVES

### 4.1 Overall Objective

- i. This study aims to evaluate the safety and efficacy of tirzepatide (*Mounjaro*®) 5mg as adjunctive therapy to AID in adults with T1D in comparison with the SoC.

### 4.2 Primary Objective

- i. Evaluate the efficacy of tirzepatide (*Mounjaro*®) 5mg as adjunctive therapy to automatic insulin delivery (AID) system on continuous glucose monitor (CGM)-based percent time in the target range (TIR) in adults with T1D.

### 4.3 Secondary Objectives

- i. Evaluate the efficacy of tirzepatide (*Mounjaro*®) 5 mg as adjunctive therapy to automated insulin delivery (AID) on CGM-based glucose metrics, HbA1c, and insulin delivery in adults with type 1 diabetes (T1D).
- ii. Evaluate the efficacy of tirzepatide (*Mounjaro*®) 5 mg as adjunctive therapy to AID on anthropometric measures and body composition in adults with T1D.
- iii. Evaluate the efficacy of tirzepatide (*Mounjaro*®) 5 mg as adjunctive therapy to AID on cardio-renal outcomes in adults with T1D.
- iv. Evaluate the safety of tirzepatide (*Mounjaro*®) 5 mg as adjunctive therapy to AID in adults with T1D.

### 4.4 Safety Objectives

The study aims to assess preliminary data about the safety of the investigational medical product (IMP) (tirzepatide [*Mounjaro*®]) 5mg and its tolerability in terms of incidence of gastrointestinal side effects, hypoglycemia episodes, severe persistent hyperglycemia with ketosis, or DKA, serious adverse events (SAE) with a possible or more significant relationship to the use of the IMP (including expected and unexpected adverse drug reactions), other serious adverse events not related to the use of the IMP, and medical events of special interest (MESI) (**See Section 5.3**).

## 5. STUDY OUTCOMES

The primary endpoint will be evaluated by computing TIR over the 12 weeks after dose-escalation (See the treatment period in Table 1). Group A: tirzepatide+AID; Group B: SoC+AID (See Figure 1).

### Primary Outcome

Mean difference in 24/7 CGM percentage time spent between 3.9 and 10 mmol/L (TIR) between groups at week 16 of treatment.

### Secondary Outcomes

Secondary endpoints will be tested hierarchically to maintain the type I error at 5% in the following order

Mean difference between groups at week 16 of treatment in

Glycated Hemoglobin (HbA1C)  
 CGM-measured TIR between 0700 and 2300 (TIR7-23)  
 CGM-measured time in the tight range (TTR, 3.9 – 7.8 mmol/L)  
 24/7 CGM-measured percent time >10.0 mmol/L  
 24/7 CGM-measured percent time >13.9 mmol/L  
 24/7 CGM-measured percent time <3.9 mmol/L  
 24/7 CGM-measured percent time <3.0 mmol/L  
 24/7 Total Daily Insulin (TDI)

### Exploratory Outcomes

Mean difference between groups at weeks 8, 12, and 16 of treatment in

CGM-measured TIR between 0700 and 2300 (TIR7-23)  
 24/7 CGM-measured percent time >10 mmol/L  
 24/7 CGM-measured percent time >13.9 mmol/L  
 24/7 CGM-measured percent time <3.9 mmol/L  
 24/7 CGM-measured percent time <3.0 mmol/L  
 CGM-measured glucose variability measured with the coefficient of variation (CV)  
 24/7 Total Daily Insulin (TDI)  
 24/7 Total Daily Bolus (TDBo)

Mean difference between groups at week 16 of treatment in

Anthropometric-Body composition:

- Body weight
- Waist circumference
- Hip circumference
- Waist-to-hip ratio
- % fat mass
- Fat mass index (FMI)
- Visceral adipose tissue (VAT)
- Lean mass index (LMI)
- Appendicular lean mass index (ALMI)

Cardio-Renal:

- Low-density cholesterol lipoprotein (LDL)
- High-density cholesterol lipoprotein (HDL)
- Cholesterol non-HDL
- Triglycerides (TG)
- TG-glucose index in fasting.
- Systolic and diastolic blood pressure
- Urine albumin to creatinine ratio (uACR)
- Hepatic steatosis and fibrosis assessed by FibroScan (CAP-value and LSM)
- MASLD biomarkers, hepatic steatosis index (HIS), and fibrosis score (FIB-4).

### Other Outcomes of Interest

- Describe reported eating behavior and food intake (using the SNAQ application).
- Describe patient-reported outcomes: DTSQc (baseline)/DTSQc (last visit-end of treatment)

### Safety Outcomes

- Occurrence of clinically significant hypoglycemia and severe hypoglycemia events (see **Annex 10** for hypoglycemia classification).
- Incidence of initiation of rescue therapy for severe persistent hyperglycemia and diabetic ketoacidosis episodes.
- Incidence of gastrointestinal side effects.
- Dehydration or renal acute events.
- Adjudicated hepatic or pancreatic AEs.
- Incidence of allergic and hypersensitivity reactions.
- Mean change in heart rate from baseline to 16 weeks.
- Treatment-emergent adverse events (TEAEs).
- Early discontinuation of study drug due to AEs.

6. STUDY DESIGN

6.1 General study design and justification of design

This randomized, parallel, open-label study evaluates the safety and efficacy of tirzepatide (*Mounjaro*®) 5mg as adjunctive therapy to AID in adults with T1D. The study consists of an eligibility assessment, screening, and randomization, followed by two weeks of a baseline (run-in) period, where participants will be requested to use their SoC+AID, wear a study activity tracker (Fitbit sense 2), and log meals using the SNAQ application (98). After baseline, participants in **Group A** will undergo an up-titration phase with 2.5 mg SC of tirzepatide once a week to assess drug-related tolerability. Participants in **Group B** will continue with their SoC+AID. After the four weeks of titration phase, participants assigned to Group A will hold stable adjunctive doses of tirzepatide (5 mg SC once a week) for up to 12 weeks. During the up-titration and assessment phases, participants will continue using the activity tracker and SNAQ app as instructed by the study team (**See Figure 1**). The primary and secondary outcomes will be assessed at 16 weeks of treatment and safety and exploratory endpoints will be evaluated at weeks 8, 12, and 16 (**See Chapter 5**).

[figure not shown]

Figure 1. Study Design.

6.2 Methods of Minimizing Bias

6.2.1 Randomization

Randomization will be performed after checking the quality of the baseline data. Participants will be randomly allocated 1:1 to tirzepatide+AID or SoC+AID using the minimization method (using *Minimpy*® software, version 0.3), considering the values of the following variables: BMI (<27 and ≥27 kg/m^2), and HbA1C <7.5 and ≥7.5%).

6.2.2 Blinding procedures

Not applicable

6.2.3 Other methods of minimizing bias

Not applicable

6.3 Unblinding Procedures (Code break)

Not applicable

## 7. STUDY POPULATION

### 7.1 Eligibility criteria

#### 7.1.1 Inclusion criteria

Participants fulfilling all the following inclusion criteria are eligible for the investigation:

- 1) Participants with diagnosed T1D for at least 12 months.
- 2) Aged between 18 to 65 years old (inclusive).
- 3) Currently on AID therapy for at least three months.
- 4) HbA1C  $\geq 6.5\%$  and  $\leq 10\%$ .
- 5) BMI  $\geq 23$  kg/m^2.
- 6) Willing to use once-weekly tirzepatide for at least 16 weeks (including up-titration)
- 7) Willing to wear a Dexcom G7 Sensor and share devices (AID) data uploads.
- 8) Willingness not to start any new non-insulin glucose-lowering agent during the trial (including metformin/biguanides, pramlintide, DPP-4 inhibitors, sodium-glucose cotransporter 2 inhibitors [SGLT2 inhibitors], and nutraceuticals).
- 9) A stable weight ( $\pm 5\%$ ) in the last 90 days or more before the screening and agree to not initiate a diet and/or exercise program during the study to reduce body weight other than the lifestyle and dietary measures for diabetes treatment.
- 10) Females with childbearing potential and males (if apply) must be willing to use reliable contraceptive methods (for the contraceptives study guidelines. **See Annex 7**)
- 11) An understanding and willingness to follow the protocol and signed informed consent.

#### 7.1.2 Exclusion criteria

The presence of any of the following exclusion criteria will lead to the exclusion of the participant:

##### Medical Conditions.

- 1) History of diabetic ketoacidosis requiring hospitalization in the past six months.
- 2) History of severe hypoglycemic event (Level 3, defined as seizure or loss of consciousness) in the past six months.
- 3) Uncontrolled Diabetic retinopathy or maculopathy
- 4) Severe gastroparesis.
- 5) Less than 12 months of insulin treatment.
- 6) Estimated glomerular filtration rate (eGFR) lab value below 30 mL/min/1.73 m^2 by the CKD-EPI formula(99).
- 7) Pregnancy or intention to become pregnant during the trial (**See annex 7**).
- 8) Currently breastfeeding or planning to breastfeed.
- 9) Currently uncontrolled seizure disorder.
- 10) History of allergy to GLP-1RAs/GIP-RA, or its excipients.
- 11) Personal or family history of multiple endocrine neoplasia type 2 (MEN-2) or medullary thyroid carcinoma.
- 12) Screening calcitonin above or equal to 35 ng/L.
- 13) Planned any surgery during the study duration.
- 14) Have uncontrolled hypertension (systolic BP above or equal to 160 mmHg and/or diastolic BP above or equal to 100 mmHg). If a participant is on anti-hypertensive therapies, doses must be stable for 30 days before screening. For participants with uncontrolled hypertension at the screening visit, antihypertensive medication may be started or adjusted.
- 15) Personal history of one of the following cardiovascular conditions (within 2 months before the screening): acute myocardial infarction, cerebrovascular accident (stroke), unstable angina, or hospitalization due to congestive heart failure (CHF).
- 16) Conditions that may increase the risk of induced hypoglycemia, such as CHF with NYHA Functional Classification III or IV or adrenal insufficiency.
- 17) Have a history of documented human immunodeficiency virus (HIV) infection.
- 18) Have an uncontrolled cardiac arrhythmia based on an electrocardiogram (ECG) at the screening time and investigator's discretion.
- 19) Cystic fibrosis.
- 20) Patient with a history of gastric bypass (bariatric) surgery, sleeve gastrectomy, or restrictive bariatric surgery, such as *Lap-Band*® or gastric banding.
- 21) Uncontrolled thyroid disease as judged by the investigator

- 22) Serum triglycerides >5.7 mmol/L (500 mg/dL) at the screening. If a participant is on lipid-lowering therapies, doses must be stable for 30 days before screening.
- 23) Personal history of acute or chronic pancreatitis. A participant with a history of acute pancreatitis caused by gallstones may be included in the study if the participant has had a cholecystectomy to resolve the problem.
- 24) Acute or chronic hepatitis other than MASLD.
- 25) Have a history of symptomatic gallbladder disease within the past 2 years (unless the participant has had a cholecystectomy to resolve the problem).
- 26) History of malignancy requiring chemotherapy, surgery, or radiation (other than basal or squamous cell skin cancer, in situ carcinomas of the cervix, or in situ prostate cancer) in the previous five years.
- 27) Active or unstable major depressive disorder (MDD) or other severe psychiatric disorder (such as known drug or alcohol abuse, diagnosed eating disorder, or any other uncontrolled psychiatric disorder) that, in the investigator's opinion, may preclude the participant from following and completing the protocol.

Prior/Concomitant Therapy:

- 28) Treatment with non-insulin glucose-lowering agents other than metformin (on a stable dose 30 days before the study)
- 29) Weight loss medications in the past three months.
- 30) Participants who are anticipated to receive, are receiving or have received within three months before the screening (>2 weeks and  $\geq 10$ mg prednisolone-equivalent) chronic systemic glucocorticoid therapy (excluding topical, intraocular, intranasal, single intraarticular injection, or inhaled preparations).
- 31) Have current treatment with (or history of, within three months before screening) medications that may significantly affect glucose metabolism.
- 32) Use of investigational drugs within five half-lives before screening.

Other exclusions

- 33) Participation in another study with an investigational drug within the 30 days preceding and during the present study.
- 34) Current enrollment in another clinical trial unless approved by the investigator of both studies and if the clinical trial is a non-interventional registry trial.
- 35) Have evidence of a significant active, uncontrolled medical condition or a history of any medical problem capable of constituting a risk when using the study devices or interfering with following study procedures or the interpretation of data, as judged by the study physician at screening.
- 36) The enrolment of the investigator, his/her family members, employees, and other dependent persons.

The study physician/investigator will assess each eligibility criteria and decide to include the participant in the trial (ICH GCP 4.3.1). This decision will be documented before the participant receives the first study intervention.

## 7.2 Recruitment and screening

Participants will be recruited at the investigator's clinic. Recruitment flyers targeting patients will be placed in waiting rooms and other suitable locations. Interested people can connect directly with the study team to express their interest in participating. The study team will perform a short interview based on the "recruitment checklist" on the phone or during a clinical visit to evaluate their eligibility. This data is not recorded in the electronic case report form (eCRF) since eligible and motivated individuals will be invited to a screening visit. During this visit, open questions related to the study will be clarified. After signing the informed consent form, eligibility will be assessed. Then, baseline data is collected (these will be included in eCRF). For more information about the screening procedures **see Section 9.3**.

Participants will receive compensation of CHF 200 for their participation, split into 50 CHF for each on-site visit. Travel fees (public transport 2nd class and/or kilometers driven by car, including parking fees) will be reimbursed separately, with an upper limit of about 50 CHF per visit.

## 7.3 Assignment to Study Groups

Randomization will be done by an independent person (not belonging to the study team) after confirming the quality of the data collected at baseline. We will perform the randomization at a ratio of 1:1 (tirzepatide+AID=21; SoC+AID=21), with the minimization method (100) using *Minimpy*® software,

version 0.3, considering the values of the following variables: BMI (<27 and ≥27 kg/m^2) and HbA1C <7.5 and ≥7.5%).

#### **7.4 Criteria for withdrawal/discontinuation of participants**

Participation in this research is voluntary. Participants may withdraw at will at any time. When withdrawing from the study, the participant should let the research team know that he/she wishes to withdraw. The participant is not required to provide a reason.

The investigator must stop the study intervention for the individual participant if any of the following criteria are met:

- Withdrawal of informed consent
- Confirmed pregnancy.
- Actively trying to become pregnant.
- Developing an allergic reaction to tirzepatide.
- If the inclusion and exclusion criteria are no longer met.
- Non-compliance with the study procedures, or
- At the investigators' judgment due to safety concerns (**See Subsection 9.4.1** for the definition of adverse events and other safety-related events).

After withdrawal, the participant will be given instructions on how to safely stop using the IMP and, eventually, on how to return to the previous treatment regimen correctly and safely. Instructions are also given on who to contact if any questions or concerns arise after study withdrawal. Any data collected until study withdrawal will remain coded for the analysis.

Withdrawn participants will not be replaced. However, at the investigator's discretion, re-screening is allowed within the recruitment period to complete 42 participants. Further information about the follow-up procedures is available in **Subsection 9.2.5**.

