## 9.2.5 Assessments in participants who prematurely stop the study.

### Individual participant-stopping criteria.

Study drug administration may be stopped for any of the following reasons:

- Three or more episodes (separated by at least 120 minutes) of clinically significant hypoglycemia (Level 2) within one day (defined as 00:00 – 23:59) of the study, after excluding other causes such as the omission of meals, unexpected increases in physical activity, or exercise (or any other contributing factor more likely than the IMP) (**See Annex 10**).
- One or more episodes of severe hypoglycemia (Level 3) (**See Annex 10**).
- One or more DKA events unrelated to the participant's AID system malfunction.
- Adjudicated hepatic or pancreatic AEs.
- Incidence of allergic and hypersensitivity reactions.
- If a participant misses three or more consecutive doses of tirzepatide due to intolerable GI symptoms (e.g., nausea, vomiting, or diarrhea) that could be reasonably attributed to the study drug, despite the mitigation plan (**See Annex 8**).
- If a participant is diagnosed with an active or untreated malignancy (other than basal or squamous cell skin cancer, in situ carcinomas of the cervix, in situ, or grade group 1 [that is, Gleason 6 or lower] prostate cancer) after randomization.
- Dehydration or renal acute events.
- Post randomization calcitonin value  $\geq 35$  ng/L and increased at least 50% over baseline.
- Supraventricular arrhythmias and cardiac conduction disorders.
- If a female participant becomes pregnant.
- Investigator decides that, in the interest of the patient, it is not medically acceptable to continue participation in the study.
- Participants with a normal BMI at baseline will be closely monitored during clinical visits. The medication will be reduced to 2.5 mg or discontinued if there is a weight gain that exceeds 5% of total body weight or if weight reduction is too rapid (defined as greater than 1% of total body weight per week) following clinical evaluation

**Table 1** describes the time points of assessment. For the definition of these AEs/SAEs and for follow-up and procedures for participants who prematurely stop the study, see **Subsection 10.1.2**.

Criteria for suspending or stopping the study.

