#### Hypersensitivity Events

The investigator will report all allergic or hypersensitivity reactions as either AEs or SAEs if any serious criterion is met. Additional data, such as the type of reaction and treatment received, will be collected on any AEs or SAEs that the investigator deems related to the study drug via an eCRF created for this purpose. The study drug should be temporarily interrupted in any individual suspected of having a severe allergic reaction to the study drug. At the investigator's discretion, the study drug may be restarted when/if deemed safe. If the study drug is permanently discontinued, the patient will continue in the trial to collect all planned efficacy and safety measurements.

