## **Annex 8. Mitigation plan for gastrointestinal symptoms**

To mitigate GI symptoms and manage patients with intolerable gastrointestinal (GI) AEs during the escalation period (Weeks 0 to 8), the investigator should:

- Advise patients to eat smaller meals, such as splitting three daily meals into four or smaller meals and stop eating when they feel full.
- Prescribe symptomatic medication (for example, anti-emetic or antidiarrheal medication) per local availability and individual patient needs.
- Symptomatic medication will be registered as concomitant medication in the eCRF.
- Temporarily interrupt tirzepatide (omit one dose; the patient will take three of four doses at that dose level). After the interruption, restart at the same dose with the patient taking medication to alleviate their GI symptoms.
- The data related to the temporary interruption of study treatment will be documented in source documents and entered on the eCRF.

In case of intolerable GI symptoms or events persist despite the above measures, the investigator may decide to discontinue the study drugs or make a de-escalation back of the study drug. However, all patients will be encouraged to use a maximally tolerable study dose of up to 5 mg SC per week.

Patients who permanently stop the study drug will continue participating in the study according to the protocol to collect all planned efficacy and safety measurements. In the event of intolerable persistent GI symptoms that occur after the escalation period (Week 8), the investigator should take the above measures to keep the patient on the study.

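### The rule that participants who stop tirzepatide stay in the trial is stated for only two kinds of event, so CGM after other drug stops may be lost from the ITT analysis

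*Protocol*

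**What the plan says.** Two places in the protocol say what happens to the data of someone who permanently stops the drug. Under Hypersensitivity Events in 10.1.2, "the patient will continue in the trial to collect all planned efficacy and safety measurements". In the gastrointestinal plan, Annex 8, "Patients who permanently stop the study drug will continue participating in the study according to the protocol", again for all planned efficacy and safety measurements.

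Three other sections deal with the same situation without that rule:

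- **7.4** treats withdrawal and discontinuation together. It opens its list with "The investigator must stop the study intervention for the individual participant if any of the following criteria are met". After the list it goes straight to "After withdrawal, the participant will be given instructions on how to safely stop using the IMP", and it provides for keeping data collected up to study withdrawal.
- **9.2.5** is headed "Assessments in participants who prematurely stop the study", but its list begins "Study drug administration may be stopped for any of the following reasons". For follow-up it refers to 10.1.2.
- **9.3.8** places a discontinuation visit at the time the drug is stopped, with the assessments of visit 4, and a phone call for safety two weeks later. It does not say whether scheduled visits and CGM continue. At visit 4 (9.3.6) all study devices are returned.

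The primary endpoint is TIR over the 12 weeks after dose escalation (chapter 5, 9.2.1). The ITT set is everyone randomised, as allocated, and is used for efficacy (11.4.1). Missing data are not imputed (11.5).

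**The concern.** An all-randomised analysis protects the comparison only if the outcome is measured on everyone, including those who stopped the drug. With no imputation, a participant without CGM in the treatment period adds nothing to the primary analysis, whatever the set is called. Only the tirzepatide arm can stop tirzepatide, so any loss from this cause falls on one side. If the people lost did less well than those who stayed, the TIR difference is overstated. No later analysis can recover sensor data that were never collected, so the rule has to be clear in the protocol and cannot be left to the SAP.

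**Working it through.** **1. Which drug stops are covered by the stay-in-trial rule**

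- Hypersensitivity: stated in 10.1.2.
- Gastrointestinal intolerance: stated in Annex 8, to which 9.2.5 and 10.1.2 refer.
- Pancreatitis: 10.1.2 says the drug must be discontinued and is silent on later efficacy data.
- Raised calcitonin: 10.1.2 foresees a possible restart, which presupposes that the patient is still in, but does not mention continued collection.
- Hypoglycaemia, ketoacidosis, hepatic, renal and arrhythmia events, and weight change: stop reasons in 9.2.5 or 10.1.2, with no statement on efficacy data afterwards.
- Pregnancy and withdrawn consent: clear exits from the study (7.4, 8.6, 10.1.2.5).

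**2. One event under three sections.** "Developing an allergic reaction to tirzepatide" is a mandatory stop in 7.4, in a list followed by withdrawal wording. In 9.2.5 it is a reason for which the drug may be stopped. In 10.1.2 a suspected severe reaction is a temporary interruption, "the study drug may be restarted when/if deemed safe", and the patient stays in the trial after permanent discontinuation.

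**3. The plan's sample size, to obtain the standard error.** Inputs from 11.2: SD 15, correlation 0.7, pre-post differences 10.5 and 0.2, two-sided 5%, power 80%, attrition 20%.

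- Effect: 10.5 − 0.2 = 10.3 points.
- Residual SD under ANCOVA: 15 × √(1 − 0.7²) = 10.71.
- n per arm: 2 × (1.96 + 0.8416)² × 10.71² / 10.3² = 16.98, so 17.
- With attrition: 34 / 0.8 = 42.5, which matches the stated 42 to within rounding.
- Standard error at 17 per arm: 10.71 × √(2/17) = 3.67 points.

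**4. Size of the bias.** Assumptions, none of them from the documents: k of the 21 in the tirzepatide arm stop, contribute no treatment-period CGM, and would have had no benefit.

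- If 10.3 is the effect in those who stay on drug, the all-randomised effect is 10.3 × (21 − k)/21 and the overstatement is 10.3 × k/21.
- If 10.3 is the all-randomised average, the overstatement is 10.3 × 21/(21 − k) − 10.3.

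| k lost | First reading | Second reading | Share of SE 3.67 |
|---|---|---|---|
| 1 | 0.49 | 0.52 | 0.13 to 0.14 |
| 2 | 0.98 | 1.08 | 0.27 to 0.29 |
| 4 | 1.96 | 2.42 | 0.53 to 0.66 |

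The bias is zero if stopping is unrelated to outcome. It is about half the table values if stoppers keep half the benefit, or if they stop at week 10 and their first 6 of 12 treatment weeks count. It is larger if they end below no benefit: at 5 points below, with 4 lost, 15.3 × 4/21 = 2.91.

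**5. Sensors.** A participant who stops right after randomisation has up to 16 weeks left, which is 112 days. At one sensor per 10 days, 112/10 = 11.2, so up to 12 sensors. A completer is already planned to use that many.

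**The case against.** The strongest reply is that the rule exists and can be reached. Section 7.4 refers to 9.2.5, which refers to 10.1.2 and, for gastrointestinal stops, to Annex 8. The Annex 8 sentence is worded for anyone who permanently stops the drug. Section 9.3.8 calls its visit additional and ties it to stopping the drug, not the study. The sentence after the list in 7.4 can be read as describing someone who leaves the study while still on drug. Gastrointestinal effects are the most recognised reactions (3.7) and are most frequent early in treatment, so the likeliest stops are covered.

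Much of this stands, and it limits the point. A reader might infer that the protocol ends CGM at drug stop or removes stoppers from the ITT set. The documents do not say so, and nothing in them states that collection ends. A reader might also take a bias of 1 to 2.4 points as expected. That needs 2 to 4 participants lost, all without benefit and without treatment-period CGM, although stops for gastrointestinal and allergic reasons already fall under the rule.

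What does not stand is that the pointers settle the matter. The chain leads to a rule placed under two specific event types. For the others, a team following 9.3.8 as written would hold a visit modelled on the one at which devices are handed back, and then make one safety call. Treating that as the end of participation is a plausible reading.

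**Conclusion.** The point holds in a limited form. The protocol intends permanent stoppers to remain in the trial, but says so only for hypersensitivity and gastrointestinal intolerance. For other drug stops, CGM may be lost in the tirzepatide arm, under an ITT analysis without imputation.

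The size cannot be bounded from the documents, which give only a 20% overall attrition rate. If 1 or 2 of 21 are lost and had no benefit, the TIR effect is overstated by about 0.5 to 1.0 points; with 4 lost, by about 2.0 to 2.4. Both are below the standard error of about 3.7, and the bias is zero if stopping is unrelated to outcome. The change should be made because it is cheap and works only before data are lost. The primary analysis is not invalid without it.

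There is one minor related point. Section 7.4 makes no longer meeting the eligibility criteria a mandatory drug stop. Read literally, a BMI falling below 23 on treatment would trigger it, although 9.2.5 has its own graded weight rule for participants with normal BMI.

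Two further items are editorial only. Section 7.4 says withdrawn participants are not replaced and 11.5 says drop-outs are. It is tempting to infer that N is at risk, but both texts stop at 42, so N does not change. Section 8.5 cites a 9.2.6 that does not appear in the document, and no result depends on it.

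**What to change.** - **9.3.8:** state that the discontinuation visit is additional to the schedule. Anyone who stops tirzepatide for any reason, without withdrawing consent or having to leave the study (for example, pregnancy), continues scheduled visits and CGM and pump data collection to week 16, and keeps devices and sensor supply until then.
- **7.4 and 9.2.5:** align with this by separating reasons to stop the drug from reasons to leave the study. In 7.4, refer allergic reactions to the rule in 10.1.2.
- **Minor, 7.4:** limit the stop for criteria no longer met to newly arising, safety-relevant exclusions, so that a BMI below 23 is handled by the weight rule in 9.2.5.
- **Editorial:** correct the 9.2.6 reference in 8.5 and harmonise the replacement wording in 7.4 and 11.5.

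The cost is a few sentences, and up to about 12 sensors for a participant who stops early, no more than already planned for a completer. Sample size, power and visit schedule do not change.
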